#### 12f. Protection of confidentiality

Subject data will be captured on paper case report forms and scanned on site. The CRFs will be stored in a locked cabinet in a restricted-access room. Identifiers will be removed from scanned pdf copies of the CRFs prior to transferring the files to the study team's offices. All electronic data files will be password-protected and encrypted, with access limited to authorized study staff. Study subjects will be assigned random study ID numbers upon consent, and data files will contain study ID numbers only, without any other individual identifiers.

A password-protected linking file allowing medical record data to be matched to study-generated data will be maintained in a secure location, with access limited to study staff. Medical record data will be downloaded on a monthly basis. Monthly medical record datasets will include data on all patients at the study clinic, not just those included in the study, as it is not possible to select only study participants prior to downloading. As soon as datasets are downloaded, the linking file will be used to select study participants and link their records with their study identification numbers. All identifiers will then be stripped from the clinical data and records for all patients not enrolled in the study will be deleted.

#### 12g. Data safety monitoring

The proposed study will evaluate the effect on patient outcomes and treatment costs of a one-time change in service delivery strategies. The rapid initiation strategy will abide by South African national treatment guidelines, make few changes to existing procedures beyond accelerating the timing, and make no changes to treatment protocols after ART is initiated.

Data collected during the period of study team interaction with study subjects (while subjects are on site and in the care of the study staff) will be monitored weekly, except during the pilot phase when daily monitoring will be performed. Adverse events that occur during the period of interaction will be reported according to and within the time periods required by IRB policies.

After study interaction with subjects ends (typically upon dispensing of the first month's supply of ARVs), any attempt to follow patients in real time could potentially bias the study results. After study procedures associated with enrollment and ART initiation have been completed, data will only be collected passively, from review of routine medical records. All of the data used by the study that could be used to monitor patient safety after treatment initiation will be routinely collected medical record

data generated by the site itself, not by the study. The study team will have access to these data only after they have been entered into the site's electronic medical record system and then downloaded by the study's lead data analyst, which will happen on a monthly basis. UPs, AEs, and SAEs that occur during this period will therefore only come to the study team's attention at least several weeks after they occur. These will be reported according to and within the time periods required by IRB policies, but can only be reported after the study team becomes aware of the events through review of the downloaded electronic medical record data.

Because there will be no active tracing of subjects who are lost to follow up after study team interaction ends, beyond any routine tracing conducted by the study clinic, the true status of subjects who are lost to follow up will not be known. Loss to follow up will be reported in study monitoring reports but the study team will not be aware of deaths among subjects lost to follow up unless these have been reported to the study clinic by household members.

Since the sample size for the study is not large and the relatively brief duration of recruitment would minimize its impact, a formal data safety and monitoring board will not be employed. Instead, the PI will receive reports from the study site on a monthly basis describing recruitment and the primary outcome by study population and reporting on any unexpected occurrences. An interim analysis will be conducted once, when one half of the study participants in Track 1 complete follow-up (reach the primary endpoint for Track 1). Only if the p-value from unadjusted analyses of the association between randomization group and the primary outcome falls below an alpha of 0.01 in the interim analysis will the study be stopped early.

Further details on data safety monitoring are included in the data safety monitoring plan in the appendix to this protocol.

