### 6e. Follow up

#### *6e i. Direct study interaction*

Direct study interaction with Track 1 study subjects will cease as follows:

- *Rapid group (Track 1)*: upon completion of the ART initiation steps described above. For most subjects, this will be at the end of their initial visit, though some may return a second time to complete the initiation procedures (e.g. patients with TB or those requesting a delay).
- *Standard group (Track 1)*: after randomization, at which point subjects will be managed by the study site following standard procedures.

From these points on, all subjects, regardless of which type of initiation they received, will be managed by the site following its routine procedures for pre-ART and ART care. Because this study evaluates routine practice and uses retention in care as an outcome, any further study interaction with subjects would affect the results, in particular loss to follow-up. There will therefore be no post-baseline study visits, only routine care visits not involving study personnel. Standard procedures will also be implemented by the study site (not the study team) for study subjects who miss scheduled visits.

Under current guidelines, adult ART patients return for routine clinical consultation visits in months 1, 2, 3, and 6 (and six-monthly thereafter). During these visits, patients have a medical exam and receive a supply of medications. All medications will be provided by the treatment site under usual treatment guidelines. A routine viral load measurement is conducted at the 6-month visit. Patients must typically return to the clinic every 1-3 months for medication pickups, whether or not they are due for a clinical consultation.

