#### 8e. Medical record data

Most data for the study will be collected from the site's routinely maintained electronic medical records, which are maintained in an information system called Therapy Edge-HIV™. Records in this information system are typically only created once a patient starts ART. Paper-based medical records kept by the site will therefore be used to supplement the electronic medical record system as needed. The fields to be collected are listed below.

*To be used to link electronic and paper-based records to study identification number only:*

- Electronic medical record system number
- Clinic file numbers
- National ID number
- Name
- Date of birth

*All subjects at baseline (ART initiation):*

- Date of positive HIV test (if available)
- Sex
- Age in years
- Weight and height or BMI
- Date treatment eligibility determined, if reported
- Date and result of eligibility-determining CD4 count
- Date and result of TB symptom screen
- Date, type, and result of TB test(s)
- TB treatment, if relevant
- WHO stage and clinical conditions
- Date ART initiated (first dose of drugs dispensed)
- First-line regimen prescribed

*For all clinic visits for duration of study follow up, including initial visit and pre-ART visits (to be used to estimate resource utilization):*

- Date of visit
- Primary reason for visit (e.g. scheduled medical visit, medication pickup, unscheduled medical visit)
- Types of professionals seen (e.g. nurse, doctor, pharmacy assistant, counselor)
- Group and individual sessions attended (e.g. wellness course, adherence education)
- Numbers and types of all lab tests conducted (including CD4 counts and viral loads)
- Other procedures (e.g. x-rays) performed

- Medications prescribed and dispensed (ARV and non-ARV)
- Admissions for inpatient care since previous visit, if recorded
- Details of inpatient care received (facility, number of days, medications, lab tests, etc.) if recorded

*At interim and final dates of data censoring:*

- Date and result of most recent viral load test
- Status at clinic (in care / died / transferred to another site / stopped care / lost to follow up, defined as > 1 month late for last medication pickup)
- New or recurring HIV-related conditions
- Date and cause of death if applicable
- Date and result of most recent CD4 count

*Track 2 subjects only (pregnant women):*

- Gestational age at diagnosis or first ANC visit for current pregnancy if previously diagnosed
- Prior exposure to PMTCT

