Medical record data for study subjects will be downloaded from the site's existing electronic medical record system, as described above. Records in this system are created only when patients initiate ART, and thus do not capture pre-ART care (HIV tests, monitoring CD4 counts, etc.). The lead data analyst will be responsible for ensuring that study identification numbers are correctly matched to the record numbers in the MRS. In instances where the data analyst cannot match a study ID number to an electronic medical record number using only the fields in the study linking file, a query will be sent to the on-site study staff, who will access the clinic's paper-based patient files to determine whether the subject ever initiated ART and, if so, locate the correct MRS number.

For subjects in the standard group, eligibility for study enrollment can only be determined once treatment eligibility is established by CD4 count or other criterion. For these subjects, the study team will review the site's paper-based patient files on a monthly basis to determine whether and when the subject has been found eligible for treatment and if treatment has been initiated. This information will be entered onto case report forms and captured in the REDCap database as described above.

A note or tab indicating that a patient is a participant in the study will be attached to the cover of each subject's paper medical record at the study site, to assist site and study staff in locating study subjects' files should this be necessary and to ensure that site staff are aware of which patients are study participants.

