##### *12a i. Loss to HIV care*

**Risk:** The study aims to initiate on ART patients who might otherwise be lost to HIV care. Some patients lost before or after ART initiation will seek care at other sites, but many will not and will postpone or end all HIV care and treatment, some until they become more seriously ill, others forever. Although the rapid initiation strategy is expected to increase the proportion of patients who do initiate ART, there is a possibility that patients who accept rapid ART initiation will subsequently discontinue treatment at a greater rate than do those who receive standard ART initiation. Preliminary studies in South Africa suggest that the loss of treatment-eligible patients before starting ART, which is expected to decrease as a result of the intervention, exceeds loss after initiation. It is also likely that patients who discontinue

treatment soon after rapid initiation may never have started at all, had only standard initiation been offered. We therefore expect the intervention to have a net positive impact on our primary outcome, the proportion of patients who are alive, in care, and virally suppressed 10 months after testing HIV-positive or making their first HIV or ANC care visit. We cannot be certain of this result in advance, however. Because this is an evaluation of routine practice and retention in care is a study outcome, no efforts will be made to retain patients in the study, beyond those already routinely undertaken by the study site clinic as part of standard of care.

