**Protection:** As patients who are subjects of this research will be both those who remain in HIV care and those who drop out, and as the research team will have access to information about which subjects are lost, efforts must be made to return these patients to HIV care. However, since losses from HIV care are a primary outcome of this study, study staff cannot interfere with usual patient care. Upon enrollment in care at the site, patients are routinely asked to give a cell phone number and address where they can be contacted at and identify an acquaintance who can be contacted should they not be able to be reached through the previously listed means. The study site maintains a small team of loss-to-follow-up counselors trained in confidentiality and ethical issues around contacting patients. These counselors do not always have access to timely information about which patients have been lost, however. As we will be generating this data, we will work alongside to the counselors to make sure they have adequate, up-to-date information on study subjects' status and can attempt to contact the patients using standard clinic procedures if necessary. In particular, we will ensure that all patients defined as lost to follow up at their 6-month viral load monitoring visit (or by 10 months after study enrollment) are referred to the counselors to be contacted.

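### Section 12g draws safety reports after study contact from a record that begins at ART initiation, so events before ART are under-ascertained, mainly in the standard arm, and never-treated subjects miss the loss-to-follow-up referral trigger

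*Protocol*

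**What the plan says.** Protocol section 12g sets out two safety regimes. While subjects are on site with study staff, data are monitored weekly (daily in the pilot) and adverse events are reported under IRB rules. After that, UPs, AEs and SAEs "can only be reported after the study team becomes aware of the events through review of the downloaded electronic medical record data", and the download is monthly. The section places the end of contact, typically, at the dispensing of the first month's ARVs.

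Section 6e i gives a different end point for the standard group: "after randomization, at which point subjects will be managed by the study site following standard procedures". For the rapid group, contact ends when the initiation steps are complete.

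On the electronic record, section 8f ii says: "Records in this system are created only when patients initiate ART, and thus do not capture pre-ART care". Section 8e is slightly softer: "Records in this information system are typically only created once a patient starts ART". It adds: "Paper-based medical records kept by the site will therefore be used to supplement the electronic medical record system as needed".

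Section 8e also lists the status categories at censoring dates, including "lost to follow up, defined as > 1 month late for last medication pickup". Section 12a i promises that the clinic's counselors will be told of "all patients defined as lost to follow up at their 6-month viral load monitoring visit (or by 10 months after study enrollment"). It names the risk in these words: "Some patients lost before or after ART initiation will seek care at other sites, but many will not". It also reports preliminary South African evidence that loss before ART exceeds loss after it.

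**The concern.** The strategy under test shortens the interval between eligibility and ART. Untreated, eligible subjects spend that interval mostly in the standard arm. A safety source that opens only when ART starts covers the two arms unequally, and it misses the interval that the trial was set up to study.

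Two things are at stake. First, section 12g provides no data safety and monitoring board; oversight rests on monthly reports to the PI. If these draw safety events from the electronic download, events before ART will be under-counted, chiefly under standard care. Second, section 12a i accepts a duty to help return lost subjects to care. If loss is defined by a medication pickup, subjects who were known to be eligible and never received ARVs fall outside the literal definition that sets off referral.

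**Working it through.** The protocol states no figure on this point, so there is none to reproduce. The check sets the sections side by side and adds one count.

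1. **End of study contact.** Section 6e i: at randomization in the standard arm; after the initiation steps in the rapid arm, which for most subjects means the end of the first visit. The description in 12g (typically at dispensing of the first ARVs) fits most rapid subjects. It does not fit the standard arm, where the site dispenses ARVs later without study staff.

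2. **Safety source after contact.** Section 12g: the monthly download of the electronic record.

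3. **Start of that source.** Sections 8e and 8f ii: at ART initiation (8e says typically).

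4. **Combination.** In the standard arm, the time from randomization to ART start lies after step 1 and before step 3, with no reporting route assigned. A rapid-arm subject who delays, or who must first be treated for TB, has a similar gap between visits. That gap is usually shorter and affects fewer subjects if the strategy works as intended.

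5. **Length of the interval.** Section 3b gives an average of 42 days from the qualifying CD4 count to ART at the team's Johannesburg site, among those who start within 16 weeks. For a subject who never starts, the interval is the whole follow-up, at least 10 months.

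6. **Number of subjects.** Inputs from section 10: Track 1 randomized enrollment of up to 400, allocated 1:1, and 46% of eligible patients starting ART within 16 weeks.
   - Per arm: 400 / 2 = 200.
   - Standard-arm subjects with no electronic record at 16 weeks: 200 × (1 − 0.46) = 108.
   - Cross-check on the plan's own target: section 10 assumes 50% of the standard arm suppressed by 10 months. Each of those must have started ART, so at most 200 × (1 − 0.50) = 100 would have no record at 10 months. The true number would be lower, because some who start are not suppressed.

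7. **Other uses of the paper files.** Section 8f ii has standard-group paper files reviewed monthly, but the stated purpose is to find eligibility and ART start. Section 8e abstracts visits before ART, for resource use. Death and care status are collected at interim and final censoring dates. None of these is tied to the safety reporting in 12g.

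8. **Loss to follow-up.** A subject with no dispensing has no last pickup and cannot be more than a month late for one. The 10-month time point in 12a i runs from enrollment, but it still applies to those defined as lost.

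9. **Primary outcome.** Section 11a i counts every eligible subject with no six-month viral load within 10 months, for any reason, as a failure. A death or loss before ART is therefore a failure in either arm, whether or not it is noticed. The interim rule in 12g tests that same outcome, so neither analysis changes.

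**The case against.** The strongest reply is that events before ART have other ways to surface. Paper files supplement the electronic record. Section 8e lists visits before ART, inpatient admissions, and date and cause of death. Unmatched subjects prompt a check of their paper files (8f ii). The site reports unexpected occurrences to the PI monthly, and households may report deaths to the clinic (12g). This stands against any claim that such events are invisible. It does not close the gap: these routes are not tied to safety reporting, or are not systematic, or operate at censoring dates.

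The paragraph in 12g can also be read as concerned only with safety after treatment starts, and so as silent on the earlier period. That is fair, but silence leaves the same interval unassigned. The data safety monitoring plan (Appendix 6) is not shown and may add detail.

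Section 12a i further commits to keeping counselors informed of subjects' status in general, and the site's own procedures for missed visits apply to everyone. This softens the referral point. The specific referral commitment still depends on a definition that never-treated subjects cannot meet.

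Passive follow-up is a deliberate and explained choice. It is not in dispute, since reading files involves no contact with subjects.

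A reader might go further and infer that the comparison of arms is biased against rapid initiation. The documents do not support that for the primary or interim analysis (step 9). No between-arm safety test is stated, and the PI's monthly reports are described by study population, the term section 5a uses for the two tracks. A reader might also derive a spurious event ratio by dividing the planned suppression rates by 77% to get ART-start rates. The 77% cancels: (0.70/0.77) / (0.50/0.77) = 0.70/0.50 = 1.4, which is just the assumed treatment effect. The 77% also applies only to patients who remained in care. No such ratio should be quoted.

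**Conclusion.** The point holds for safety monitoring and for the loss definition. Read together, sections 6e i, 8e, 8f ii and 12g leave the time before ART without an assigned safety-reporting route, mainly in the standard arm. Deaths, admissions and SAEs in that time will be systematically under-ascertained for ongoing monitoring. Eligible subjects never dispensed ARVs also fall outside the literal trigger for counselor referral. What is affected is the monitoring reports, the descriptive safety and loss data, and subject protection; the primary outcome and interim test are not.

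The illustrative size is about 108 of 200 standard-arm subjects with no electronic record at 16 weeks. It assumes full enrollment, an even split, and that the 46% carries over to this trial. Section 3a attaches the 46% to patients who had received their CD4 results; on that reading, the share of all eligible patients starting ART could be lower and the count higher. The plan's own 50% target points the other way. The 108 counts subjects outside the electronic record, not missed events: the documents give no event rates and do not say how much the paper files would recover.

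**What to change.** - **Reconcile 12g with 6e i, 8e and 8f ii.** State when study contact ends in each arm, and name a safety source for the time between that point and ART start.
- **Use the monthly paper-file review already in 8f ii.** Add date and cause of death, hospital admission and SAE. Apply the review to every enrolled Track 1 subject not yet on ART, in both arms.
- **Report safety counts by arm**, split into before ART and on ART, with all enrolled subjects as the denominator.
- **Extend the loss definition in 8e** to subjects with no ART dispensed, for example no ART and no recorded clinic visit by 10 months after enrollment, so that the existing 10-month referral in 12a i reaches them.
- **Check Appendix 6** and align it with the revised text.

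The cost is modest extra abstraction time and some protocol wording. The review already takes place for the standard group, involves no contact with subjects, and leaves the sample size and primary analysis unchanged.

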#### **5. Study Design**

##### 5a. Overview of study design

The study will be divided into two tracks, based on the study populations to be included.

Track 1: *Non-pregnant adults*. Track 1 will be a randomized comparison of rapid initiation of ART to the current standard of care for non-pregnant, treatment eligible adults. Patients testing positive, providing a blood sample for a CD4 count, or receiving a CD4 count result will be individually randomized 1:1 to either the rapid ART initiation strategy (rapid group) or the standard ART initiation strategy (standard group). Patients in the rapid group who are found to be eligible for ART will be offered the opportunity to initiate ART in the fastest time feasible given individual circumstances, and whenever possible on the same day as study enrollment. Patients in the standard group will be offered standard treatment initiation as currently implemented by the study site.

Track 2: *Pregnant women*. Track 2 will be a programmatic evaluation of rapid initiation of ART for pregnant women. Immediate ART initiation on the day of a woman's first antenatal care visit was introduced in South Africa in a guideline revision in April 2013 and is now the standard of care at the study site. Guidelines call for women to remain on ART for the duration of pregnancy regardless of their initial CD4 count. Adherence to ART during pregnancy, as measured by monthly medication pickups, will be compared to adherence before rapid initiation was offered.

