## 10. Sample Size

Track 1: In a recent study we conducted in Johannesburg, we found that among patients eligible for ART, 46% initiated ART within 16 weeks of eligibility. In an analysis of data from the same Johannesburg site, we estimated that among more than 3000 patients initiated on ART in 2010 and 2011 who remained in care, 77% were virally suppressed at the routine 6-month viral load. We would thus expect approximately  $0.46 \times 0.77 = 35\%$  of those eligible to have both started treatment and be virally suppressed by the 6-month viral load. For our study site we conservatively estimate that 50% of those eligible for treatment in the standard group will be suppressed by 10 months after their HIV test. We anticipate that the rapid initiation strategy will increase the proportion suppressed to 70%.

For our primary analysis, using an  $\alpha$  of 0.05, power of 90%, 1:1 randomization, and an uncorrected Fisher's exact test, we would need to enroll 124 HIV positive ART-eligible subjects per group (248 total). We expect 70% of all HIV-positive patients to be eligible for ART under current South African guidelines on the day they test positive for HIV or make their first HIV care visit, based on results from published studies in South Africa. Therefore to reach 124 subjects per arm who are treatment eligible on the day of testing we will need to consent 177 subjects per group (354 total). To allow stratification in the analysis by sex and by site, we will consent up to 300 per group (600 total) to have adequate power. We will enroll in the study up to 67% of this total (enrollment=400).

The sample size for the Track 1 retrospective comparison group will be 120. This group will be limited to patients already found to be eligible for ART at one of the two study sites (Thuthukani). They will be compared with each of the two randomized prospective groups (rapid and standard). We expect that Thuthukani will account for approximately 60% of total prospective enrollment of 400, or 120 in each of the randomized prospective groups. We will thus aim to enroll the same the number of subjects into the retrospective comparison group as in each prospective group.

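### The Track 1 interim look can stop the trial at p<0.01 with no visible reduction of the final 0.05 level, and its meaning is unclear if enrolment has already ended

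*Protocol*

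**What the plan says.** Protocol section 10 sizes the Track 1 primary analysis with an alpha "of 0.05, power of 90%, 1:1 randomization, and an uncorrected Fisher's exact test". It assumes 50% suppressed in the standard group ("we conservatively estimate that 50% of those eligible for treatment in the standard group will be suppressed by 10 months") and expects that "the rapid initiation strategy will increase the proportion suppressed to 70"%. The result is 124 eligible subjects per group, 248 in total. Enrolment may go up to 400 so that results can be stratified by sex and site.

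Section 12g dispenses with a formal monitoring board and plans a single interim analysis of the primary outcome, when half of the Track 1 participants have reached the endpoint. The trial stops early only if the unadjusted p-value "falls below an alpha of 0.01 in the interim analysis will the study be stopped early". The section gives no direction for the rule, does not say what stopping would cover, and refers to a monitoring plan in an appendix for further detail.

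Section 11b analyses crude risk ratios with 95% confidence intervals. Section 11a i places the primary endpoint 10 months after enrolment. No section states how long recruitment will last; section 12g says only that it is fairly short.

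**The concern.** A comparative look that can end the trial on a significant result is a second chance to reject the null hypothesis. If 0.01 is used at the look and the full 0.05 remains for the final test, the two chances together exceed 5%. The protocol itself fixes both levels, so this is not a detail merely left to the analysis plan.

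The second difficulty is timing. Section 12g describes the intervention as a one-time change in service delivery, and it is given at or soon after enrolment. The look must wait for 10-month outcomes in half the subjects. If everyone has been randomized by then, stopping cannot protect future participants. What is left to stop is follow-up by passive record review, and the protocol does not say whether that would end.

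**Working it through.** **1. Reproduce the plan's sample size.** Inputs from section 10: 50% versus 70%, alpha 0.05 (taken as two-sided), power 90%, 1:1 allocation. With mean proportion 0.60, the uncorrected chi-square formula is

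n = [1.960 × √(2 × 0.6 × 0.4) + 1.2816 × √(0.5 × 0.5 + 0.7 × 0.3)]² / 0.20² = [1.3579 + 0.8692]² / 0.04 = 124 per group.

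This matches. The continuity-corrected (Fisher-like) version gives 134 and a one-sided test gives 101. Power at 124 is 90.0%, so 124 is a fixed, single-look size that uses the whole two-sided 0.05.

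**2. Overall type I error.** The look is at information fraction 0.5 (section 12g), so the two test statistics have correlation √0.5. Counting a crossing at either analysis as a positive result,

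1 − P(|Z1| < 2.576 and |Z2| < 1.960) = 0.0546.

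The result depends little on timing: 0.0567 at fraction 0.3 and 0.0522 at 0.7.

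Exact binomial enumeration, null rates 0.50 to 0.70:

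| Test at both looks | 124 per group | 200 per group |
|---|---|---|
| Uncorrected chi-square, 0.01 then 0.05 | 5.2 to 5.6% | 5.3 to 5.5% |
| Fisher's exact, 0.01 then 0.05 | 3.8 to 4.0% | 4.1 to 4.3% |

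For the chi-square test the look adds 0.4 to 0.5 points to the error of the final test alone.

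**3. Final level that restores 5%.** Solving the expression in step 2 with 0.01 at the look gives a final two-sided level of 0.0452 (|z| > 2.003). Discreteness remains: with that level the exact chi-square error is 5.0 to 5.3% at 124 per group and 4.7 to 5.2% at 200.

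**4. Power over both looks at 50% versus 70% (exact, chi-square).** At 124 per group it moves from 89.9% to 89.4%; at 200 per group, from 98.5% (98.45) to 98.4% (98.38).

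**5. When the look falls.** Assume uniform accrual over T months. Half the subjects are enrolled at T/2 and reach the endpoint at T/2 + 10. The look is at or after the end of accrual when T/2 + 10 ≥ T, that is, T ≤ 20.

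| Accrual T (months) | Look at month | Enrolled of 400 |
|---|---|---|
| 6 | 13 | 400 |
| 12 | 16 | 400 |
| 18 | 19 | 400 |
| 20 | 20 | 400 |
| 24 | 22 | 367 |

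Finishing in 20 months needs 400/20 = 20 enrolled per month over two sites. Section 5b says Thuthukani starts about 840 non-pregnant adults on ART a year, or 70 a month, and the second site nearly 10,000 adults a year. Section 10 expects about 240 of the 400 from Thuthukani, which is 12 a month over 20 months.

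**6. Chance of crossing 0.01 at the look, true rates 50% and 70%.** With 248 enrolled (62 per group at the look): 38% by chi-square, 32% by Fisher. With 400 enrolled (100 per group): 63% by chi-square, 58% by Fisher.

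**The case against.** **The test.** Section 10 names Fisher's exact test. Used at both looks, its conservatism absorbs the extra chance and the attained error stays below 5%. This stands, and a reader who infers that the 5% rate is broken whatever the test goes too far. But section 10 calls the test uncorrected, its sample size is that of the chi-square test, and section 11b reports risk ratios with 95% intervals, so the protocol does not settle on the conservative test.

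**The missing appendix.** Section 10 gives 0.05 as a sample-size input, section 11b states no final significance level, and the monitoring plan is not shown. That no alpha at all is set aside for the look is therefore a reading of the visible text and cannot be proved from it.

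**The size.** The excess is about half a percentage point and would rarely change a conclusion. This also stands.

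**Likelihood of stopping.** A reader might infer that an early stop is the expected outcome. That holds only near the ceiling of 400, which section 10 words as an upper limit; at 248 the chance is below one half.

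**Timing.** No accrual period is stated, and section 6b ii allows recruitment to be staggered because of equipment capacity. Completion before the look is plausible from the site volumes but remains an inference.

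**Loss of data.** A reader might infer that stopping would discard up to half the outcomes. The protocol does not say so: outcomes come from routine clinic records, and section 6e ii continues follow-up until a final censoring date.

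**Monthly reports.** A reader might also take the reports to the principal investigator as giving outcomes by arm. The text has them "describing recruitment and the primary outcome by study population and reporting on any unexpected occurrences", and sections 5a and 11a ii use population for non-pregnant adults and pregnant women. No defect is shown there.

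**Conclusion.** The concern holds in a limited form. As far as the visible text goes, an interim stopping level of 0.01 is combined with an unreduced 0.05. For the chi-square or risk-ratio analysis the nominal overall two-sided error is about 5.5% instead of 5%. The exact chi-square range is 5.3 to 5.5% at 200 per group and slightly wider at 124. The figure assumes a look at half the information, a two-sided test, a crossing at the look counted as a positive finding, and no adjustment in the appendix. With a true Fisher's exact test at both looks the error is about 3.8 to 4.3% and there is no excess.

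The stopping rule also lacks a defined consequence. If accrual takes 20 months or less, the look cannot spare anyone randomization, yet under the planned effect it crosses with a probability of about 38% (248 enrolled) to 63% (400 enrolled). That is frequent enough for the meaning of a stop to be written down beforehand.

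Severity is minor to moderate: a small numerical excess and an undefined action, both cheaply settled.

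**What to change.** In section 12g, keep the look at 0.01 and state that the final primary analysis is tested at a two-sided 0.045, with 95.5% confidence intervals to match. Repeat that level in sections 10 and 11b, and name one test for both looks. If the monitoring plan already contains an adjustment, refer to it in these sections instead.

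State that all subjects already randomized are followed to 10 months and included in the primary analysis whatever the look shows, so that an early stop can end only further enrolment. Give the expected accrual period, so that the reader can see whether any enrolment would remain at the look.

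Settle this before the interim data are seen, because a final level chosen afterwards would carry little weight. The cost is a paragraph of text and about 0.5 points of power at 124 per group or 0.1 at 200, with no change in sample size.
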